### Sample size

We have designed this trial to detect a 12.5% relative difference in the mean number of ANC components measured and recorded over the two visits (eight total) between the control and the intervention (control mean = 4, intervention mean = 4.5, an absolute difference of 0.5). This difference is based on 1) the mean number of ANC components measured in the formative phase, which was 1.95 (standard deviation 0.9) for a single visit (doubled for the sample size calculation to account for the two-visit primary outcome) and 2) a pragmatic decision regarding the time and resources available for recruitment. Using an intra-cluster correlation coefficient (ICC) of 0.05 [34] and assuming an average cluster size of 20 women, 52 clusters, 1,040 pregnant women (520 in each arm) will have 90% power to detect a 12.5% relative increase in the mean number of ANC components over the two visits in the intervention arm compared to the control arm (control mean = 4.0, intervention mean = 4.5). Allowing for a 20% loss to follow-up, we will enroll 1,320 women (660 in each arm) across 66 clusters.

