Recognising that the trial is not powered to detect effect differences in subgroups, we will conduct exploratory subgroup analyses for the primary outcome to determine if the intervention effect varies by the following pre-specified subgroups: age (split at the median); parity (0/1 or more); caste or tribe (yes/no); highest education level completed (completed primary or above/other); EDSS use (used for entire ANC consultation/not used for entire consultation) and gestational age at first visit (< 10 week/10 week or above). Within the pre-specified subgroups, we will assess heterogeneity of treatment effect with a test for interaction [5–9]. Interaction test p-values will be presented but will be interpreted with caution, due to the exploratory nature, the multiple tests performed and the low power of the interaction test. We will estimate beta coefficients along with 95% CIs for each subgroup. As this is an exploratory analysis of potentially influential characteristics, we will not hypothesise effect directions.

The primary outcome data with missing values will be handled under two different assumptions. First, the primary outcome will be considered as complete if it is confirmed that the participant attended the facility for the second visit. Data missing for both of these visits will be assumed and coded as component ‘not done’. Second, the primary outcome will not be considered as complete if the second visit data is missing and it is confirmed that the participant did not attend for this visit. In this case, participants’ data will not be included in the primary analysis.

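### Effect modification by age and gestational age is tested only on two-group splits, which loses information if the modification is gradual (minor; exploratory analyses only)

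*Protocol article*

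**What the plan says.** The subgroup paragraph of Statistical methods in the protocol article opens: "Recognising that the trial is not powered to detect effect differences in subgroups, we will conduct exploratory subgroup analyses for the primary outcome". Six subgroup factors follow. Two of them are measured on a continuous scale and are cut into two groups: "age (split at the median" and "gestational age at first visit (< 10 week/10 week or above".

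The test is tied to those groups: "Within the pre-specified subgroups, we will assess heterogeneity of treatment effect with a test for interaction". The article promises a coefficient and a 95% confidence interval for each subgroup. It says that interaction p-values will be read cautiously "due to the exploratory nature, the multiple tests performed and the low power of the interaction test".

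No continuous interaction is described for either covariate, and no reason is given for the 10-week cut. Gestational age at enrolment, a related but different variable, is already an adjustment covariate in the primary model.

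**The concern.** A sample median cannot be found without numeric ages, and a 10-week cut cannot be applied without gestation in weeks. The fuller information is therefore available and would go unused in the test. If the intervention effect drifts with age or gestation, a two-group comparison treats women on the same side of the cut as identical, and the interaction test loses power.

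The stake is limited. A real gradual modification is more likely to be missed, and a non-significant interaction says even less than the plan already concedes. The primary result does not depend on it.

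**Working it through.** **The plan's own figure.** The Sample size section takes "control mean = 4, intervention mean = 4.5, an absolute difference of 0.5" and a formative-phase mean "which was 1.95 (standard deviation 0.9) for a single visit", doubled for two visits. This gives a difference of 0.5 and an SD of 1.8. With two-sided alpha 0.05 (assumed; not stated) and 90% power:

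- n per arm = 2 × (1.960 + 1.282)² × 1.8² / 0.5² ≈ 273.
- Design effect = 1 + 19 × 0.05 = 1.95, so 273 × 1.95 ≈ 532 per arm, against 520 stated (power at 520 is 89.4%).
- 1,040 / 0.8 = 1,300 women or 65 clusters; 66 clusters, for equal arms, give 1,320.

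The main-effect calculation reproduces within 3%. The article gives no power figure for the interaction tests.

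**How low the two-group power is.** Assume the covariate varies within clusters and 1,320 × 0.8 = 1,056 women are analysed. For a split with share p in one group, SE = 1.8 × √0.95 × √[4/(Np) + 4/(N(1−p))]. An interaction of 0.5, as large as the design main effect, would have 64% power at p = 0.5, 46% at p = 0.2 and 28% at p = 0.1. The plan's statement about low power is fair.

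**Information kept by a split.** If the effect changes linearly with covariate X, and X has the same distribution in both arms, the efficiency of the two-group test relative to the continuous test is the squared correlation between X and the group indicator:

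- Normal X: φ(z_p)² / [p(1−p)].
- Uniform X: 3p(1−p).

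*Age, median split (p = 0.5):*

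| Assumed shape | Efficiency | Lost |
|---|---|---|
| Normal: 0.3989² / 0.25 | 0.637 | 36% |
| Uniform: 3 × 0.25 | 0.75 | 25% |
| Normal (mean 24, SD 4) truncated at 18, simulated | 0.66 | 34% |
| Right-skewed from 18, simulated | 0.55 | 45% |

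*Gestational age, 10-week cut, normal X, by assumed share below 10 weeks:*

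| Share below | Efficiency | Lost |
|---|---|---|
| 30% | 0.576 | 42% |
| 20% | 0.490 | 51% |
| 10% | 0.342 | 66% |
| 5% | 0.224 | 78% |

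If gestational age were uniform over 6 to 28 weeks, the share below 10 would be 4/22 = 18% and the loss 1 − 3 × 0.18 × 0.82 ≈ 55%.

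**Effect on power.** Power after the split = Φ[(z_power + 1.96) × √efficiency − 1.96].

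| Power, continuous test | Eff. 0.637 | Eff. 0.490 | Eff. 0.342 |
|---|---|---|---|
| 80% | 61% | 50% | 37% |
| 30% | 21% | 17% | 13% |

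The second row matters because the plan expects low power: the absolute fall is then 9 to 17 percentage points, not 19 to 43.

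**The opposite case.** If the true modification is a step exactly at the cut, the two-group test loses nothing. Because the correlation is symmetric, the linear test is then the one that loses the fractions above.

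**The case against.** The plan misstates nothing here. It labels the analyses exploratory, concedes that the trial is not powered for them and promises cautious reading. Two-group estimates with confidence intervals are a conventional display, and no stated decision rests on the tests. The analysis plan is not shown and may already include a continuous test. All of this stands and keeps the priority low. It does not explain why the test itself should use only the groups.

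Prompts that are specific to each visit could also produce steps rather than a straight line. That is fair and is the reason for a shape check, but the article gives no ground for a step at 10 weeks or at the sample median age.

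Three stronger readings are tempting, and the document supports none of them:

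- *That the median split invites selective cutting.* The rule is fixed in advance and depends on age alone, not on outcome or arm. Only the cut value is unknown beforehand.
- *That the gestational-age groups must be very unequal because women may enrol up to 28 weeks.* The subgroup is defined by gestation at first visit, and the model's adjustment for previous antenatal visits shows that some women are expected to enrol later than that. If first visit means the first antenatal visit, the enrolment window does not give the share below 10 weeks.
- *That gestation at enrolment is the correct modifier.* Early or late entry to care is a different question, and replacing one variable with the other would change what is asked.

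**Conclusion.** The point holds as a minor improvement. The article fixes the interaction tests for age and gestational age on two groups and describes no continuous alternative. Under gradual modification the age test loses about 36% of its information if age is normal and 25% if uniform. The gestational-age test loses about 42% to 78% if gestation is normal and between 30% and 5% of women fall below 10 weeks.

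These sizes rest on assumed distributions, assumed shares and a linear modification, none of which the document supplies. A reader might infer that a definite fraction of the information is lost; the document does not allow that, and under a step at the cut the loss is nil. The primary analysis, the sample size and the trial's main conclusion are unaffected.

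**What to change.** Specify that the interaction tests for age and for gestational age at first visit use the covariate as a continuous term: linear, with a spline check of shape. Keep the median and 10-week groups, with their estimates and 95% confidence intervals, for display. An interaction with gestational age at enrolment may be added, since that variable is already in the model, but it should not replace the stated modifier.

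The cost is a sentence or two in the analysis plan and one shape check per covariate. No new data are needed. If the analysis plan already does this, confirming it closes the point.

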**Fig. 3 Fig3:**
[figure not shown]
Schema for evaluating the effect of mIRA EDSS

Facilities randomized to the control arm will continue to provide ANC services as per the existing standards of care. Evidence-based guidelines in the form of posters/pamphlets on the current national and state guidelines pertaining to the screening and management of PIH, GDM, and anaemia, and routine ANC procedures will be provided to all facilities in both the study arms.

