### Blinding

Because of the nature of this intervention, pregnant women, healthcare providers, and field research staff collecting the outcome data will be aware of allocation to the intervention or control arm, precluding blinding. However, adequate measures will be taken to avoid possible bias by the field research staff. The field research staff stationed at the facilities in the intervention arm during the lead-in period (an intensive support period described later) will be switched to the control arm before recruitment of women starts. The field research staff will also be trained to reduce the risk of observer bias while conducting the ANC observations. The team analyzing the data and interpreting the trial results will be masked to the study arm until all analyses outlined in the statistical analysis plan are completed.

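### EDSS use is listed as an interaction subgroup, but no control woman can be in the used level, so the interaction and the effect in that level cannot be estimated

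*Protocol article*

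**What the plan says.** The Statistical methods section of the protocol article sets out exploratory subgroup analyses of the primary outcome "to determine if the intervention effect varies by the following pre-specified subgroups". Five of the six factors are characteristics of the woman: age, parity, caste or tribe, education, and gestational age at first visit. The sixth is "EDSS use (used for entire ANC consultation/not used for entire consultation"). The same commitments cover all six: "Within the pre-specified subgroups, we will assess heterogeneity of treatment effect with a test for interaction", and "We will estimate beta coefficients along with 95% CIs for each subgroup". The section makes no exception for EDSS use. Its caveats are that the p-values need caution "due to the exploratory nature, the multiple tests performed and the low power of the interaction test".

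On who has the software, the text following Fig. 3 under Intervention delivery says "Facilities randomized to the control arm will continue to provide ANC services as per the existing standards of care". The sections on intervention delivery, training and implementation describe training, installation and on-site support for intervention facilities only.

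On timing, women are recruited after randomisation and the lead-in. The Monitoring section tells field staff not to step in when a provider leaves the tablet aside during an observed consultation. Use is therefore settled by the provider, after randomisation, at the consultation where the outcome is recorded.

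The Blinding section says that the analysis team "will be masked to the study arm until all analyses outlined in the statistical analysis plan are completed".

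**The concern.** A treatment-by-subgroup interaction asks whether the difference between arms changes across levels of a factor. Both arms must be represented at each level. Five of the listed factors meet that condition. EDSS use does not, because it describes delivery of the intervention itself.

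Two things are at stake. First, the promised test and the promised coefficient for the full-use level cannot be produced. Second, statistical software usually drops the redundant term and still prints an estimate, which could be reported as the planned result. What it prints is a comparison of consultations in which the provider did or did not use the tablet throughout. The outcome counts what that same provider did at the same consultations. A conscientious provider plausibly does both, so the estimate could look like a dose-response in favour of the EDSS even if the EDSS did nothing.

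**Working it through.** **1. Identifiability.** Code A = 1 for the intervention arm and U = 1 for use throughout the consultation. The interaction model is

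E(Y) = b0 + b1·A + b2·U + b3·A·U.

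The control arm has no EDSS, so U = 0 whenever A = 0. Then A·U = U for every woman, and the last two columns are identical. With 660 women per arm (Sample size section) and one simulated draw at 60% use (assumed), the cells are:

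| | Full use | Less than full use |
|---|---|---|
| Control | 0 | 660 |
| Intervention | 372 | 288 |

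The four-column design matrix has rank 3. Only b2 + b3 can be estimated, never b3 alone. This follows from the empty cell and holds at any uptake and any sample size. If a few control consultations did use the software through contamination, b3 would rest entirely on them.

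**2. What remains after the redundant term is dropped.** There are three groups: control, intervention with full use, and intervention without. The coefficient on U is the difference between the last two, within one arm and not randomised. The coefficient on A compares the less-than-full-use part of the intervention arm with the whole control arm, which is not randomised either.

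**3. Scale for an illustration.** The plan's own figure is reproduced first, to settle the SD. A single-visit SD of 0.9 is given, and doubling it for two visits gives 1.8. With difference 0.5 and two-sided alpha 0.05 (assumed, not stated):

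- n per arm before clustering = 2 × (1.960 + 1.282)² × 1.8² / 0.5² = 272.4, rounded up to 273
- design effect = 1 + (20 − 1) × 0.05 = 1.95
- 273 × 1.95 = 532 per arm, against 520 stated; power at 520 per arm is 89.4%, against 90% stated.

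The plan's figure reproduces closely, so SD 1.8 and ICC 0.05 are its working values. The between-cluster SD is √0.05 × 1.8 = 0.40.

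**4. Illustrative bias with no true effect.** The simulation had 66 clusters of 20, SD 1.8 and ICC 0.05. The chance of full use in a cluster was set by logit(p) = 0.4 + 1.5 × latent trait, which gives about 57% use. The trait had correlation r with the cluster's outcome level. The link and r are assumptions.

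| r | Full use minus control | Less than full use minus control | Gap |
|---|---|---|---|
| 0 | −0.01 | 0.01 | −0.01 |
| 0.3 | 0.05 | −0.07 | 0.12 |
| 0.6 | 0.11 | −0.13 | 0.24 |
| 1.0 | 0.18 | −0.23 | 0.42 |

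The gap depends on how tightly use follows the trait. In the limiting case where the trait alone decides use, at 60% use, its correlation with a woman's outcome is at most √0.05 = 0.22. Full use then shows 0.644 × 0.2236 × 1.8 = +0.26, the rest shows −0.966 × 0.2236 × 1.8 = −0.39, and the gap is 0.65. Here 0.644 and 0.966 are the normal density at the 60% cut, 0.386, divided by 0.6 and 0.4.

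If use also tracks quality within clusters, the correlation can exceed 0.22. At 0.3 the same formula gives +0.35 and −0.52, a gap of 0.87.

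**The case against.** The strongest defence is that little depends on this analysis. It is one of six exploratory subgroups, the article says the trial is not powered for them, and it promises cautious reading of the p-values. The primary analysis is by randomised arm. The article nowhere says it will replace the failed interaction with an as-treated contrast and read that causally. All of this stands, and it limits the severity. It does not remove the point: caution about power and multiplicity does not help with a parameter that the design cannot estimate. Nor is this a detail left to a statistical analysis plan, because the article itself fixes EDSS use as an interaction subgroup.

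A reader might go further in four ways that the documents do not support.

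- **That the trial's conclusion is at risk.** It is not. The sample size, the primary estimate and the secondary outcomes do not use this variable.
- **That the bias is known to be about 70% of the target (0.35 / 0.5).** That needs 60% use and a correlation of 0.3, neither of which is in the article. A purely cluster-level trait cannot reach 0.3 at the planned ICC of 0.05. The calculation also treats the second level as non-users, whereas its wording can include partial use.
- **That a complier-average effect with arm as instrument repairs the analysis.** Intervention providers also receive refresher ANC training, a workshop covering routine ANC procedures and 20 days of on-site support, and some will use the EDSS in part. Each could change the outcome without full use at the observed visit, so the exclusion restriction is doubtful.
- **That the masking commitment is certainly broken.** Tabulating EDSS use by arm would identify the intervention arm, which sits badly with "will be masked to the study arm until all analyses outlined in the statistical analysis plan are completed". The analysis plan is not shown, however, and may order the work so that this comes last.

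**Conclusion.** The plan is wrong as written on this item. The interaction test for EDSS use is not identifiable, and the full-use level has no control group from which to estimate a treatment effect. This conclusion needs only the fact that the EDSS is confined to intervention facilities.

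The direction and size of bias in any substitute contrast are less certain. Bias towards the EDSS is likely, because use and outcome are both provider behaviour at the same visit. The illustrative gap of about 0.1 to 0.4 components, against the 0.5 target, rests on an assumed link between use and cluster quality. A tighter link, or dependence within clusters, would make it larger, and no dependence would make it zero. The documents cannot narrow this.

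A lesser ambiguity is that the primary outcome spans two visits, while the factor refers to a single consultation. A woman with full use at one visit only is not clearly classified.

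Severity is moderate to low: one exploratory analysis is invalid and the primary analysis is unaffected.

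**What to change.** Remove EDSS use from the list of interaction subgroups in the Statistical methods section. Report it descriptively as intervention-arm fidelity in the process evaluation, which already draws on monitoring visits and EDSS usage data, and state how use is classified across the two visits.

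If an analysis of effect by use is still wanted, specify it separately, run it after the masked analyses are complete, and label it non-randomised. State its assumptions. For a complier-average analysis, these must address how refresher training, on-site support and partial use may breach the exclusion restriction.

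The deletion costs one line of wording. It needs no new data and leaves the sample size and the primary analysis unchanged.

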### Process evaluation

A mixed-methods process evaluation will be nested within the trial assessing intervention effectiveness. The overall aim of the process evaluation is to generate evidence to inform the interpretation of the outcomes of the main trial, and to further understanding of the theories underpinning mIRA EDSS quality improvement interventions.

As part of the parallel mixed-method process evaluation [36], data for quantitative and qualitative analyses will be collected at multiple time points throughout the trial. Quantitative data collection methods will include ongoing routine monitoring from all sites. A baseline facility survey will be conducted for facilities in both trial arms to examine the role of structural quality and organizational factors in moderating the intervention process and effects. Monitoring data from in-person research staff visits to the facilities in the intervention arm and backend data from the mIRA EDSS will be used to evaluate the frequency and quality of use of mIRA. As mIRA will be implemented alongside existing paper-based record-keeping systems, we will conduct an audit of record-keeping practices to examine change in completeness and accuracy of the ANC register and MCP cards before and after mIRA EDSS implementation. Qualitative data collection methods will include regular debriefing meetings and field notes from field research staff involved in the trial implementation and end-line in-depth interviews with selected healthcare providers who used the mIRA EDSS; policymakers and research staff involved in the implementation of the intervention.

### Economic evaluation

We will conduct an economic evaluation to estimate the additional costs of the intervention relative to the value of the improved health outcomes achieved by calculating the additional cost of the intervention and the use of resources for providing ANC in the intervention and control arms.

The cost of the enhanced ANC intervention includes the cost of the mIRA EDSS, and the training costs incurred to facilitate the integrated management of patients by healthcare providers. Healthcare resource use will also change if the intervention is successful. While for some women, improved management will avoid some future costs, healthcare resources used by others will increase as a consequence of receiving care that they would not have received in the absence of the intervention. Thus, the net impact might be to either increase or decrease costs. The improved health outcomes will be estimated using trial data on the number of ANC components received by women; the proportion of women identified with GDM or PIH; the proportion of women with GDM or PIH whose blood sugar and pressure are controlled to recommended targets (in both the control and intervention arms). This information will be combined with data from the literature to estimate the additional QALYs generated by the intervention. The final step is to combine the changes in resource use and the changes in health outcomes in a single measure that can potentially be compared with the cost-effectiveness of other interventions for this patient group, or other patient groups.

